##### Primary outcome

Our primary outcome is the utilization of medical or vocational rehabilitation services 12 months after random assignment. This information is stored in the individual pension insurance account and will be provided by the German Pension Insurance North.

##### Secondary outcomes

Our secondary outcomes are employment, receipt of unemployment benefits, receipt of sickness benefits, and disability pensions 1 year after random assignment. These data are stored in the individual pension insurance account and will be provided by the German Pension Insurance North. Data on employment, unemployment, and sickness benefits will be reported in days per month.

##### Tertiary outcomes

*Physician visits:* The use of primary medical care is captured by asking for visits to general practitioners and other specialists, as well as hospitalizations [25].

*Psychosocial health:* Psychosocial health is measured with three scales of the HEALTH-49 (Hamburger Modul zur Erfassung allgemeiner Aspekte psychosozialer Gesundheit für die therapeutische Praxis) [17]. We address depression (six items [e.g., suffering from a feeling of hopelessness]), phobic anxiety (five items [e.g., suffering from anxiety or fear about leaving the house]), and interactional difficulties (seven items [e.g., suffering from difficulties showing feelings]) in the past 2 weeks. All items are 5-point scaled (0 = not at all, 1 = somewhat, 2 = moderately, 3 = quite a lot, and 4 = very much). The three total scores are the unweighted means of the corresponding items, with higher values indicating higher levels of impairment.

*Self-reported prognosis of employability:* A brief self-reported measure is used to assess the expected impairment of future employment [18]. Feasibility and psychometric properties of the score were tested thoroughly [18, 26]. The total score is based on answers to three questions: Do you believe that you will be able to continue working until you reach retirement age (certainly, rather yes vs. uncertain, and in no case)? Do you see your current state of health as a permanent threat to your general ability to work (no vs. yes)? Are you currently considering applying for a pension (disability pension) (no vs. yes)? The binary categorized answers are summed to give a total score between 0 to 3, with higher scores indicating a higher risk of permanent work disability.

*Limitations on participation*: We use an abbreviated version of the IMET (Index zur Messung von Einschränkungen der Teilhabe) to assess limitations on participation in eight areas of life (e.g., daily tasks and responsibilities, such as work, school, and household chores) that were derived from the International Classification of Functioning, Disability, and Health. The single items are answered on a scale from 0 to 10, with minimum and maximum representing not impaired and completely impaired [19].

*Health state:* To assess the general health of participants, the 5-level EQ-5D is used [20]. Respondents are asked to indicate their health state by answering questions on five different dimensions: mobility, self-care, usual activities, pain/discomfort, and anxiety/depression. Each dimension has five response levels: no problems, mild problems, moderate problems, severe problems, and extreme problems. A combination of numbers represents a health state, with 11,111 reflecting no problems on any of the five dimensions. The 5-digit health state is then transformed to an index value, which reflects how good or bad this health state is according to the preferences of the German general population [27].

*Perceived stress:* The Perceived Stress Scale (PSS-10) is a widely used and well-established self-report scale for measuring perceived stress [21]. Respondents are asked 10 questions about thoughts and feelings that have occurred in the past month (e.g., How often have you felt nervous and stressed in the last month). Participants indicate on a 5-point scale (never, almost never, sometimes, quite often, or very often) how often they had these feelings in the last month. In addition to a total perceived stress score (0 to 40 points), one score is determined for helplessness (0 to 24 points) and one for self-efficacy (0 to 16 points). Higher values indicate more perceived stress.

*Social support:* To evaluate the degree of perceived social support, we use the brief form of the Perceived Social Support Questionnaire (F-SozU K-6, Fragebogen zur Sozialen Unterstützung) [22]. The respondents are asked to rate six statements that assess support from the social environment (e.g., having a very trusted person whose help one can always count on). Statements are rated with a 5-point scale, ranging from 1 (does not apply) to 5 (exactly applicable). The total score is calculated by averaging the single ratings.

*Life satisfaction:* We use eight items of the German Socio-Economic Panel to assess satisfaction in seven life areas (e.g., health or work) and with life itself [23]. Responses are 11-point scaled ranging from 0 (totally dissatisfied) to 10 (completely satisfied).

*Information about services supporting participation:* Four items are used to assess knowledge about services supporting participation (financial support, medical rehabilitation, vocational rehabilitation, and services for participation in society). Participants rate from 0 (strongly disagree) to 5 (strongly agree) whether they are informed about these services.

*Work ability*: Self-reported work ability is assessed using the single-item Work Ability Score, which asks for current work ability compared with lifetime best [24]. The score ranges from 0 (completely unable to work) to 10 (work ability at its best). Higher scores indicate better work ability. The Work Ability Score is highly correlated with the entire Work Ability Index score [28, 29].

*Work participation*: We assess employment state (employed vs. unemployed) and the job title to describe work participation. In addition, we also ask for sickness absence (current state and duration in the past 12 months).

##### Other measures

Age and gender are derived from administrative records. Additional sociodemographic data is assessed by questionnaire and relates to the native language, partnership, children, and educational level.

#### Observational study

*Delivered dose:* As part of the observational study, case managers document the intervention components (i.e., telephone counseling, one-on-one interview, and the case management intervention) in a standardized manner using computerized sheets.

*Received dose:* We use the same items assessing knowledge about services supporting participation as in the randomized controlled trial also in the observational study. In addition, we ask which of these services were initiated. Furthermore, the participants rate five statements about how individual needs and goals were identified, five statements about their relationship with the case manager, three statements about the case manager’s competence, five statements about goal attainment, and nine statements about contents of the case management intervention. Ratings of these statements use a 4-point scale from 0 (do not agree) to 3 (completely agree). Finally, we also ask the participants to rate the different components of our multi-component strategy (e.g., the telephone contact), with grades from 1 (very good) to 5 (insufficient).

### Participant timeline

Table 3 shows the full schedule of enrollment, interventions and assessments.

**Table 3 Tab3:** Schedule of enrollment, intervention, and assessments

*Timepoint*	*Pre-intervention*	*Beginning of intervention*	*End of intervention*	*12-month follow-up*
**Enrollment**				
Screening and postal information	X			
Randomization	X			
**Interventions**				
Telephone counseling		X		
Initial one-on-one interview		X		
Case management		Continously		
**Assessments**				
Baseline questionnaire		X		
Questionnaire at the end of the case management intervention			X	
12-month follow-up questionnaire				X
Computerized documentation by case managers		Continously		

### Sample size

We will include 9000 persons (intervention group: *n* = 4500; control group: *n* = 4500) in order to detect an increase in claiming a rehabilitation from 10 to 12% in the intervention group (two-sided type I error rate: 5%, power: 80%). We expect that 12.5% of individuals who are informed about our case management intervention will contact our case managers. Of whom, half will join the one-on-one interview, and of whom, 80% will start a case management intervention. This is in line with our pilot study showing that about 5% of the informed individuals participated in a case management intervention. About half of them are anticipated to claim rehabilitation.

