### Recruitment

To identify individuals who are at increased risk of receiving a disability pension, the German Pension Insurance North transfers pseudonymized administrative data to the University of Lübeck. In addition to the personal identification number, this data set contains age, gender, and nationality, as well as income and the duration of receipt of short- and long-term unemployment benefits, and sickness benefits for the past 3 years. We summarize these data into a standardized and validated risk index score with a mean of 50 points and a standard deviation of 10 points [6]. High scores indicate an increased risk of receiving a disability pension. Of individuals with a risk index score of at least 60 points, a random sample is drawn. This sampling is done twice: 4500 people are identified in 2021, and another 4500 people will be identified in 2022. In total, 9000 individuals with a high risk index score will be selected for our study. These individuals are randomly assigned equally to the intervention or control group in both years. The samples are transmitted to the German Pension Insurance North who informs the intervention group in several waves about the case management intervention. A total of 225 individuals are targeted for participation in case management and will be accompanied by an observational study.

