### Data collection

Outcomes are collected using administrative data from the German Pension Insurance North, patient questionnaires and computerized documentation by case managers (Tables 2 and 3). The administrative data capture our primary and secondary outcomes of the randomized controlled trial completely, reliably, and validly for both the intervention and control group participants. These data are transmitted electronically, encrypted and pseudonymized by the German Pension Insurance North to the University of Lübeck. The patient questionnaire to assess tertiary outcomes of the randomized controlled trial will be sent out 12 months after random assignment by the German Pension Insurance North with a return envelope addressed to the University of Lübeck. The questionnaires of the observational study are handed out to the participants by the case managers and returned to them completed or handed out together with a return envelope addressed to the University of Lübeck. The computerized case manager documentation was developed with the case managers to ensure the feasibility of the documentation, and all case managers were trained on the required documentation before the randomized controlled trials began. Case managers send their computerized documentation of the telephone counseling, the one-on-one interview, and the case management intervention weekly to the researchers, who check it for completeness and validity. The patient forms and computerized documentation of the case managers were tested in a previous pilot study. If participants withdraw their consent, the collected data will be deleted.

The use of administrative data will ensure complete coverage of primary and secondary outcomes from all study participants. Moreover, we created a website to transparently inform study participants about the study and to maintain interest in the study. Three weeks after the first mailing of the 12-month follow-up questionnaire a single reminder is sent, again containing the questionnaire and the return envelope addressed to the University of Lübeck.

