### Statistical methods

We will use Cox regressions to analyze our primary outcome and our time-to-event secondary outcome (i.e., disability pension) and report hazard rate ratios and 95% confidence intervals. Poisson regressions with baseline adjustments will be calculated to estimate incidence rate ratios and 95% confidence intervals in our analysis of our continuous secondary outcomes. We will use linear regressions to analyze our continuous tertiary outcomes. The use of administrative data will ensure that all individuals can be included in our analysis as randomized (intention-to-treat).

Subgroup analyses examine whether estimates differ for the first and second cohorts of participants. The analysis of our nested cohort study of case management participants only will describe the implementation of the case management intervention and changes during the case management intervention. We will use paired t-tests for continuous outcomes and McNemar tests for binary outcomes when analyzing the change between the start and end of the case management intervention.

Analyses of our primary and secondary outcomes will not be affected by non-responses or patient withdrawals due to the use of administrative data, but tertiary outcomes may be missing due to non-response or incomplete response to the 12-month follow-up questionnaire. We will use multiple imputation to augment incomplete responses to the 12-month follow-up questionnaire.

We will not perform interim analyses and did not specify a stopping rule. Statistical test will be regarded as significant if the two-sided p-value of a test is less than 0.05. An up-to-date version of Stata (StataCorp, College Station, Texas, USA) will be used to conduct analyses.

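### The stated 80% power does not match 4500 per arm for 10% versus 12%: those inputs give about 86%, a minor and conservative misstatement

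*Protocol article*

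**What the plan says.** The Sample size section gives all the inputs together. The size is "We will include 9000 persons (intervention group: *n* = 4500; control group: *n* = 4500"). The effect, error rate and power follow in the same sentence: an "increase in claiming a rehabilitation from 10 to 12% in the intervention group (two-sided type I error rate: 5%, power: 80"%). It does not describe 80% as a minimum, and it names no inflation factor.

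Three other sections complete the inputs:

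- **Recruitment** confirms 1:1 allocation: "These individuals are randomly assigned equally to the intervention or control group in both years".
- **Primary outcome** fixes the time point: "Our primary outcome is the utilization of medical or vocational rehabilitation services 12 months after random assignment".
- **Statistical methods** names the analysis: "We will use Cox regressions to analyze our primary outcome". It also rules out interim analyses, so no type I error is spent before the end.

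On losses, Data collection says: "The use of administrative data will ensure complete coverage of primary and secondary outcomes from all study participants". Statistical methods adds that non-response and withdrawal will not affect the primary analysis.

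The Sample size section also sets out an uptake chain: 12.5% of those informed make contact, half of these attend the interview, and 80% of those start case management. About half of the starters are expected to claim rehabilitation. Recruitment gives a target of 225 case management participants.

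**The concern.** Sample size, control rate, intervention rate, error rate and power are all stated, and any four of them determine the fifth. Here the fifth does not follow: the stated 80% is about 6 percentage points below what the other four give, and the stated 4500 is about 17% above what 80% requires.

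An undeclared attrition margin would be the usual explanation. The article excludes it in effect by saying that administrative records supply the primary outcome for everyone. What is at stake is the accuracy of a published design figure. The trial's ability to detect its target effect is not at risk.

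**Working it through.** **Inputs.** n = 4500 per arm, p1 = 0.10, p2 = 0.12, two-sided 5%, stated power 80% (all Sample size); 1:1 allocation (Recruitment); no loss of the primary outcome (Data collection, Statistical methods); Cox regression (Statistical methods). The mean rate is 0.11. Normal quantiles are 1.960 and 0.8416.

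**1. Can the stated pairing be reproduced?** Two-proportion test, pooled variance under the null:

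n = [1.960·√(2·0.11·0.89) + 0.8416·√(0.10·0.90 + 0.12·0.88)]² / 0.02²
= [0.8673 + 0.3722]² / 0.0004
= 1.5363 / 0.0004 ≈ 3841 per arm (7682 in total).

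So 4500 / 3841 = 1.17, or 17% more than needed. With continuity correction the requirement is 3941, and 4500 / 3941 = 1.14.

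**2. Power at 4500 per arm.**

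- Null standard error: √(2·0.11·0.89/4500) = 0.006596, times 1.960 = 0.012929.
- Alternative standard error: √(0.1956/4500) = 0.006593.
- z = (0.02 − 0.012929)/0.006593 = 1.073, so power is 85.8%.
- With continuity correction (subtract 1/4500 from the difference): z = 1.039, so power is 85.1%.

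**3. The planned Cox analysis.** Under proportional hazards, 10% versus 12% at 12 months implies HR = ln(0.88)/ln(0.90) = 1.213. Expected events are 450 + 540 = 990. By the Schoenfeld formula, z = (√990/2)·ln(1.213) − 1.960 = 1.082, so power is 86.0%. For 80% power, 840 events are enough (846 by Freedman), which is about 3818 to 3845 per arm.

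**4. Other conventions.** Per-arm requirement, with 4500 as the figure to match:

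| Convention | n per arm |
|---|---|
| 80%, unpooled variance | 3839 |
| 80%, arcsine | 3835 |
| 80%, one-sided | 3026 (3125 with correction) |
| 80%, risk ratio 1.20 used as the hazard ratio | 4295 to 4318 |
| 85%, pooled | 4394 (4493 with correction) |

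No 80% convention gives 4500. The 85% figure with continuity correction comes closest.

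**5. Attrition.** Getting from 3841 to 4500 would need a loss of 1 − 3841/4500 = 14.6% (12.4% from 3941). None is stated.

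**6. Difference that does match 80%.** Solving the power formula at 4500 per arm with a 10% control rate gives 11.84%, a difference of 1.84 points instead of 2.00.

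**7. The uptake chain.** 0.125 × 0.50 × 0.80 = 0.05, and 0.05 × 4500 = 225, the Recruitment target. If the remaining 95% of the arm stay at 10%, the arm rate is 0.95 × 10% + 0.05 × 50% = 12.0%, the planned rate.

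**The case against.** **The size may come from elsewhere.** Five per cent of 4500 is exactly the 225 case management participants targeted. The number may have been set by that target and then found to satisfy an 80% criterion. This is plausible, but the article does not say it: it presents 9000 as the size needed for 10% versus 12% at 80%. A condensed article may omit the reason for choosing a larger number. That does not make the stated power correct for the stated inputs.

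**A rough convention may explain 80%.** Treating the risk ratio of 1.20 as a hazard ratio gives 81.8% power with 990 events, close to the stated figure. However, a hazard ratio of 1.20 takes 10% to 11.88%, not 12%, and it needs about 4300 per arm, not 4500. It may show where the figure came from, but it does not reproduce the sentence.

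**The error is harmless in direction.** This stands in full. The design meets and exceeds its stated power, and nothing is biased.

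**Two stronger readings are tempting, and neither is supported.**

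- A reader might infer that the extra 6 points are the trial's only reserve against dilution by people who never take up case management. The article's own uptake chain yields 12.0% for the whole arm, so the 2-point difference is already the diluted intention-to-treat effect. Uptake below the assumed 5% would be a separate risk.
- A reader might infer that a null result would be misinterpreted. Statistical methods commits to 95% confidence intervals, and what a null result excludes would be read from those. The 80%-power difference also moves only from 2.00 to 1.84 points.

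**Conclusion.** The point holds as a minor correction to a stated figure. For 4500 per arm, 10% versus 12% and two-sided 5%, power is about 86% (85.1% to 86.0% across the two-proportion test, its continuity-corrected form and the Cox analysis), not 80%. Eighty per cent needs about 3841 per arm, or 3941 with continuity correction.

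This rests on 1:1 allocation, individual randomisation, a complete primary outcome and, for the Cox figure, proportional hazards with 990 events. The first three are stated or described in the article; proportional hazards is an assumption made here, and the 990 events follow from the stated rates. Whether 80% is a slip for 85% or 4500 came from the case management target cannot be settled from the article.

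**What to change.** Restate the power sentence along these lines: 4500 per arm give about 86% power to detect 10% versus 12% at a two-sided 5% level, equivalently 80% power to detect 10% versus about 11.84%. If the number was chosen so that 5% uptake yields 225 case management participants, add that as the reason for exceeding the minimum. The cost is one or two sentences, with no change to enrolment, allocation or analysis.

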### Recruitment

To identify individuals who are at increased risk of receiving a disability pension, the German Pension Insurance North transfers pseudonymized administrative data to the University of Lübeck. In addition to the personal identification number, this data set contains age, gender, and nationality, as well as income and the duration of receipt of short- and long-term unemployment benefits, and sickness benefits for the past 3 years. We summarize these data into a standardized and validated risk index score with a mean of 50 points and a standard deviation of 10 points [6]. High scores indicate an increased risk of receiving a disability pension. Of individuals with a risk index score of at least 60 points, a random sample is drawn. This sampling is done twice: 4500 people are identified in 2021, and another 4500 people will be identified in 2022. In total, 9000 individuals with a high risk index score will be selected for our study. These individuals are randomly assigned equally to the intervention or control group in both years. The samples are transmitted to the German Pension Insurance North who informs the intervention group in several waves about the case management intervention. A total of 225 individuals are targeted for participation in case management and will be accompanied by an observational study.

### Allocation

The principal investigator (MB) generates random numbers using Stata 16.0 to split both random samples of people with a risk index score of at least 60 points (one in 2021 and one in 2022) into the intervention or control group. Allocation is concealed from the case managers, who are not aware of group assignments until participants contact them. Sample selection and random assignment by the principal investigator uses a data set with pseudonyms. This data set is provided by the German Pension Insurance North electronically. After randomization, the principal investigator transmits the pseudonyms and group assignment also electronically to the German Pension Insurance North. Only the pension insurance agency can link pseudonyms to actual individuals to inform them about the intervention, to collect primary and secondary outcomes from administrative records and to contact participants to send them questionnaires to gather tertiary outcomes. Enrollment for the nested observational study is done by the case managers.

